## Abstract

**Background:**

Platelet-rich plasma (PRP) has been widely used in the treatment of rotator cuff tendinopathy. Due to the lack of unified standards for PRP preparation and clinical instructions, its efficacy remains controversial.

**Purpose:**

We aimed to conduct a pragmatic comparison of two commonly used composite PRP formulations with different platelet (PLT) and leukocyte concentrations to provide clinical evidence for the optimal PRP formulation in the treatment of rotator cuff injury (RCI).

**Methods:**

A prospective, single-center, participant-blinded, outcome-assessor-blinded, and statistician-blinded randomized controlled trial with a 12-month follow-up investigating PRP in RCI will be conducted at Southwest Medicine University. Participants who choose PRP treatment will be randomly allocated in a 1:1 ratio to either group. Clinical assessments will be performed at baseline (2 days before PRP injection) and 1, 3, 6, and 12 months after the first injection. The primary outcomes include the Chinese version of the Constant-Murley Score (CMS) and the visual analog scale (VAS). Secondary outcomes include imaging changes assessed by magnetic resonance imaging (MRI) and ultrasound (US) scanning, serum cytokine measurements, the 12-Item Short Form (SF-12), and adverse events (AEs). Statistical analysis will be performed according to the intention-to-treat (ITT) principle.

**Implications:**

The results will provide new evidence for the optimal PRP formulation for RCI in clinical practice. Furthermore, we will investigate multiple outcomes, including clinical, functional, structural, and inflammatory changes after PRP injection.

**Trial registration:**

https://www.chictr.org.cn/searchproj.html?title=&officialname=&subjectid=®status=®no=ChiCTR2500113374&secondaryid=&applier=&studyleader=&createyear=&sponsor=&secsponsor=&sourceofspends=&studyailment=&studyailmentcode=&studytype=&studystage=&studydesign=&recruitmentstatus=&gender=&agreetosign=&measure=&country=&province=&city=&institution=&institutionlevel=&intercode=ðicalcommitteesanction=&whetherpublic=&minstudyexecutetime=&maxstudyexecutetime=&btngo=btn, This study was registered in the Chinese clinical trial registry (ChiCTR2500113374).

## Introduction

1

Rotator cuff injury (RCI) is a prevalent musculoskeletal disorder, with prevalence ranging from 5 to 39%, leading to intense shoulder pain, aberrant shoulder movement, and progressive muscle atrophy (1). When selecting the optimal treatment for patients with symptomatic RCI, clinicians should take tear size, shoulder function and stability, and patient preferences into full consideration (2). Currently, with the rapid development of arthroscopy, surgical repair can relieve pressure on the injured rotator cuff; however, postoperative pain and tendon-bone healing outcomes remain variable (1, 2). The focus of the current trend has shifted toward biological enhancement rather than simple mechanical repair (3). The clinical application of various biological agents, such as platelet-rich plasma (PRP), stem cells, or purified exosomes, has been widely explored in the treatment of tendinopathy (4–7).

PRP, an autologous blood product containing a high concentration of platelets (PLTs), has been widely used in RCI (8). Once PLTs in PRP are activated, p-granules undergo degranulation and then release growth factors (GFs) and cytokines that can modulate the microenvironment (9). With supraphysiological concentrations of PLTs, pathological tissues can mimic the initial stages of healing to rapidly enhance repair signals during the inflammatory phase (10). In addition, GFs can promote vascularization and stimulate angiogenesis along with cell proliferation (10–13).

Theoretically, PRP can promote rotator cuff tendon healing. However, controversies surrounding its efficacy may arise from variables throughout the process—from manufacturing to clinical application—that can affect PRP quality and effectiveness (4, 14), such as preparation methods, PLT concentration, and cellular composition (15). The relationship between platelet concentration and its biological effect is not linear. For any given tissue, there exists a therapeutic window; concentrations below this threshold may be insufficient to stimulate a robust healing response, while concentrations above it could potentially inhibit cellular activity or promote an excessive inflammatory reaction, thereby hindering repair. For tendinopathy, the optimal PLT concentration is 3–5 times that of the physiological concentration in the whole blood (16). Beyond PLT concentration, the role of leukocytes in PRP is also controversial (17). Leukocyte-rich PRP (LR-PRP) can aggravate the inflammatory response, particularly due to pro-decomposition factors produced by neutrophils, which can accelerate the apoptosis of tendon cells and chondrocytes (18, 19). Leukocyte-poor PRP (LP-PRP), which can promote collagen formation and reduce the inflammatory environment, may be particularly suitable for acute RCI (3). Liu et al. (15) proposed that the biological status of the tendon, rather than leukocyte concentration, ultimately determines the efficacy of tendon healing.

For tendon repair, the goal is to restore the organized structure and reduce the tear rate by promoting cellular differentiation. However, which type of PRP is optimal for the treatment of RCI remains uncertain. It is essential to assess the components of PRP before injection into the injured sites and to understand the roles of different cytokines and how they relate to improvements in clinical outcomes. In this study, we aim to perform a pragmatic clinical comparison of two composite PRP formulations—low-PLT LP-PRP and high-PLT LR-PRP—with different PLT and leukocyte concentrations, both of which are widely used in clinical practice. We intend to explore the clinical efficacy of these two formulations and provide evidence for the optimal PRP formulation for RCI.

## Materials and methods

2

### Study design, randomization, and blinding

2.1

A prospective, single-center, participant-blinded, outcome-assessor-blinded, and statistician-blinded randomized controlled trial was scheduled to commence in January 2026, with a 12-month follow-up at the Affiliated Hospital of Southwest Medical University. The primary endpoint is set at 12 months after the first injection, allowing assessment of functional, structural, and inflammatory recovery. This study strictly complies with the Declaration of Helsinki and involves human participants. The study design adheres to the SPIRIT statement and is registered in the Chinese Clinical Trial Registry (ChiCTR2500113374), with ethical approval obtained from the Institutional Review Board (IRB) of the Affiliated Hospital of Southwest Medical University (KY2025570). All participants will sign a written informed consent form before enrollment, which clearly states the study purpose, intervention measures, follow-up plan, potential risks and benefits, and the right to withdraw from the study at any time without affecting clinical care.

### Participant enrollment

2.2

Patient recruitment will be conducted from January 2026 to December 2026, with a planned recruitment period of 12 months, at the Affiliated Hospital of Southwest Medical University. The inclusion criteria are as follows (20–22): (1) age between 18 and 65 years; (2) patients presenting with clinical signs of shoulder pain and dysfunction who are not candidates for surgery; (3) severity of RCI according to the Ellman classification system: grade I (<3 mm, <25% tendon thickness), grade II (3–6 mm, 25–50% tendon thickness), and grade III (>6 mm, >50% tendon thickness) as determined by magnetic resonance imaging (MRI), with a disease course of 2–6 weeks (subacute stage); (4) hemodynamic stability; (5) patients willing to undergo PRP injection therapy; and (6) patients who provide informed consent and can comply with all study procedures and requirements.

The exclusion criteria are as follows (23): (1) age <18 years or >65 years; (2) previous scapula dysfunction or shoulder joint activity disorders resulting from central or peripheral nerve injury; (3) external injury combined with an upper limb fracture; (4) patients who have undergone prior surgical intervention or plan to undergo surgical repair within 6 months; (5) patients who have received shoulder injection therapy, such as steroid injection, within 6 months; (6) patients with blood disorders, including PLT dysfunction syndrome, PLT count <100,000/μL, or hemoglobin <10 g/dL; (7) patients with fever or potential infectious disease within 2 weeks; (8) patients with systemic diseases, a history of cancer, long-term use of antiplatelet agents, habitual analgesic use, or other conditions that make them unsuitable for rehabilitation therapy or PRP injection; and (9) patients who have participated in other drug studies within 30 days.

The trial protocol is shown in Figure 1.

**Figure 1 fig1:**
[figure not shown]
Flowchart of the overall study design.

### Procedures

2.3

#### PRP intervention and basic characteristics

2.3.1

Clinically, two types of PRP are commonly used: Composite PRP formulations characterized by either a lower PLT and leukocyte concentration or a higher PLT and leukocyte concentration. The classification of PRP follows previous studies (24, 25). All included participants will receive one of the two types of PRP injections, administered randomly once a week for a total of 2 weeks.

The final PRP volume for each injection session is 2 mL. The absolute PLT count administered to each patient will be calculated by multiplying the PLT concentration measured in the final PRP product (×10^9^/L) by the injection volume (2 mL). Blood cell counts of whole blood and PRP will be analyzed using an automated hematology analyzer. PLT concentrations and absolute counts for both groups are presented in Table 1. All values will be recorded in case report forms (CRFs) for subsequent correlation analyses with clinical outcomes.

**Table 1 tab1:** Characteristics of PRP formulations and absolute platelet counts.

Group	WBC (×10^9^/L)	NEU (×10^9^/L)	RBC (×10^12^/L)	PLT (×10^9^/L)	Absolute PLT count (×10^9^/2 mL)	PLT enrichment (fold)
Group 1	0.11 ± 0.11	0	0	868.67 ± 98.51	1.74 ± 0.20	2.5–3.5
Group 2	29.29 ± 0.56	15.49 ± 1.41	0.16 ± 0.16	1329.00 ± 261.00	2.66 ± 0.52	4.0–6.0

Data are presented as mean ± standard deviation.

RBC, red blood cell; WBC, white blood cell; NEU, neutrophil; PLT, platelet.

The absolute platelet count was calculated based on a 2 mL injection volume.

PLT enrichment fold was estimated relative to the mean whole blood platelet concentration (200–300 × 10^9^/L).

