A standardized preparation procedure is an important factor influencing clinical efficacy, as it has a direct impact on the final composition and quality of PRP. PRP can be formulated in multiple ways, and there is currently no internationally accepted consensus to standardize its formulation. It seems that the concentration of PRP components produced by the machine is relatively stable. In fact, the concentrations of PLTs, leukocytes, and GFs may vary depending on the equipment used. Several factors can affect the quality of PRP products, including anticoagulant type, g-force, centrifugation duration, cell volume, and separation accuracy (40). To achieve optimal clinical effects, PRP components and doses should be tailored to the specific scenario. In this study, the PLT concentration for Group 1 is set at 2.5–3.5-fold enrichment (1.74 ± 0.20 × 10^9^/2 mL) and for Group 2 at 4.0–6.0-fold enrichment (2.66 ± 0.52 × 10^9^/2 mL), administered once per week for two consecutive weeks. Compared to higher concentrations with doses of 4–6 mL used in knee osteoarthritis, the PRP dose for tendinopathy is usually set at 2–3 mL, as the injection strategy focuses on the injured or degenerated tendons rather than the intra-articular space. This dosage scheme is based on the anatomical characteristics of the shoulder joint and clinical practice of PRP for RCI. It has been reported that a 3–5-fold enrichment of PLTs is recommended as the optimal concentration for tendinopathy (43). Higher concentrations of PRP may lead to tendon overgrowth and even cause shoulder impingement syndrome (44). Excessively high PRP concentrations may even have an inhibitory effect on cell proliferation, migration, and the production of type I collagen (45). As an important part of tissue healing, inflammatory cells such as neutrophils and monocytes migrate to the injured area and remove necrotic tissue through phagocytosis (15). The leukocyte concentration plays a crucial role in PRP function, influencing both anabolic and catabolic processes, which are often time-dependent (46). LR-PRP can induce a pronounced inflammatory response, increasing cytokine levels such as IL-6, IL-10, and TNF-α, especially TNF-α, which inhibits apoptotic cell death by activating the NF-kB signaling pathway. Therefore, LR-PRP seems to have a more effective regeneration tendency in tendon healing at the early stage (43). In contrast, LP-PRP can improve the biomechanical properties of tendons, including tensile stress and stiffness, due to its beneficial effects on tendon proliferation, collagen synthesis, and inflammation modulation (15, 47). However, in the application of LP-PRP, this approach may be more suitable for chronic tendinopathy (48). PRP-related approaches should be further refined in terms of preparation parameters to achieve the “right drug,” tailored to specific clinical indications and usage.

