Most previous studies investigated the role of leukocytes or PLTs in clinical practice. Based on current research, this study will first investigate the synergistic effects of PRP components and their concentrations, and will subsequently analyze the relationships between these factors and patient variables in a stepwise manner. This protocol reports a detailed preparation method and PRP characteristics, aiming to stimulate discussion on the optimal PRP formulations for different musculoskeletal conditions and to promote the development of standardized PRP guidelines in the future. Although this study focuses on several factors affecting the practical efficacy of PRP, many uncertainties may still exist in its clinical application, which need to be reported and investigated in further studies. Future studies should expand the sample size, extend the follow-up period, and include multi-center data to validate the results. In addition, further *in vitro* experiments are needed to explore the specific mechanism underlying the synergistic effects of PLT and leukocyte concentrations on rotator cuff tendon healing.

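### Table 1's fold-enrichment ranges do not follow from its own means and reference, the per-patient platelet count covers one of two sessions, and the Discussion claims component effects that the design cannot show

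*Protocol article*

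**What the plan says.** All places are in the protocol article.

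- **Section 2.3.1, Table 1.** Mean platelet concentration is 868.67 ± 98.51 ×10^9/L in Group 1 and "1329.00 ± 261.00" in Group 2. The absolute counts per 2 mL are 1.74 ± 0.20 and 2.66 ± 0.52 ×10^9. The fold column reads 2.5–3.5 and 4.0–6.0. The footnote states: "PLT enrichment fold was estimated relative to the mean whole blood platelet concentration", with 200–300 ×10^9/L in brackets.
- **Section 3, Discussion.** The ranges return as a description of the arms: "In this study, the PLT concentration for Group 1 is set at 2.5–3.5-fold enrichment", with 4.0–6.0-fold for Group 2.
- **Section 2.3.1, text.** "The absolute PLT count administered to each patient will be calculated by multiplying the PLT concentration measured in the final PRP product" by the 2 mL injection volume. PRP is "administered randomly once a week for a total of 2 weeks", and 2 mL is the volume for each session. The recorded values are meant for later correlation with clinical outcomes.
- **Section 2.8.** The analysis set includes randomized participants who receive at least one injection.
- **Aim.** The Abstract (Purpose) and the Introduction describe a pragmatic comparison of two composite formulations. The Discussion goes further. It says the study was designed to investigate the role of leukocytes and platelets, and that "this study will first investigate the synergistic effects of PRP components and their concentrations".

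**The concern.** The fold range is the figure a reader would set against the 3–5-fold window that the Introduction and the Discussion both cite as optimal. If it does not follow from the table's own concentrations, the contrast between the arms is misdescribed.

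The per-patient count is the natural exposure variable for the planned correlations. A rule that takes one session's concentration times 2 mL does not record how much a patient received. It uses the same formula for patients with one session and patients with two.

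Platelets and leukocytes both change between the only two arms. A difference in outcome can be assigned to the formulation, but not to either component or to their interaction. The Discussion wording invites that assignment.

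**Working it through.** **Inputs** (Table 1 and its footnote): platelet means 868.67 and 1329.00 ×10^9/L, SDs 98.51 and 261.00; WBC 0.11 ± 0.11 and 29.29 ± 0.56 ×10^9/L; reference 200–300 ×10^9/L; 2 mL per session; two sessions. The value 250 used below is an assumed midpoint. The article gives only the range.

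**1. Absolute counts (concentration × 0.002 L).**
- Group 1: 868.67 × 0.002 = 1.737, SD 98.51 × 0.002 = 0.197. Stated 1.74 ± 0.20.
- Group 2: 1329 × 0.002 = 2.658, SD 261 × 0.002 = 0.522. Stated 2.66 ± 0.52.

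Both reproduce.

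**2. Fold (mean concentration ÷ whole-blood reference).**

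| | ÷300 | ÷250 | ÷200 | Stated |
|---|---|---|---|---|
| Group 1 | 2.90 | 3.47 | 4.34 | 2.5–3.5 |
| Group 2 | 4.43 | 5.32 | 6.645 | 4.0–6.0 |

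Shortfall at the lower limits: 2.90 − 2.5 = 0.40 and 4.43 − 4.0 = 0.43. At the upper limits: 4.34 − 3.5 = 0.84 and 6.645 − 6.0 = 0.645.

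Working backwards, the stated ranges need these whole-blood values:
- Group 1: 868.67/3.5 = 248 to 868.67/2.5 = 347.
- Group 2: 1329/6 = 222 to 1329/4 = 332.

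These differ from each other and from 200–300.

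Other rules were tried: mean − SD, mean or mean + SD for either limit, over 200, 250 or 300 in every combination. None gave all four stated limits to within 0.25. For example, (mean − SD)/300 to mean/250 gives 2.57–3.47 for Group 1, which fits, but 3.56–5.32 for Group 2, which does not.

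**3. Two sessions at the Table 1 means.** Group 1: 2 × 1.737 = 3.47 ×10^9. Group 2: 2 × 2.658 = 5.32 ×10^9. The rule in the text assigns 1.74 and 2.66. (These totals equal the folds at 250 only because 2 × 0.002 = 1/250.) The between-arm ratio is 1329/868.67 = 1.53 either way.

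**4. Separability of the components if the arms were pooled (1:1 mixture).** The correlation of a component with arm is its half-difference between means divided by √(half-difference² + average within-arm variance).
- Platelets: half-difference 230.165, average variance (98.51² + 261²)/2 = 38,913, so r = 230.165/√(52,976 + 38,913) = 0.76.
- WBC: half-difference 14.59, average variance (0.11² + 0.56²)/2 = 0.163, so r = 14.59/√(212.868 + 0.163) = 0.9996.
- Platelets with WBC, assuming no within-arm correlation: 0.7593 × 0.9996 = 0.76. With an assumed within-arm correlation of −0.5 to +0.5 this is 0.75 to 0.77.

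WBC is almost the arm label itself. Some platelet variation remains within arms, but almost no WBC variation does.

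**The case against.** **The column is labelled an estimate, and the midpoint fits.** At 250 the means fall inside both stated ranges, and the paired whole-blood counts behind Table 1 are not shown. This stands as a limit on the size of the error. It does not explain the ranges, since the footnote gives 200–300 and no simple rule yields both.

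**The platelet dose is right.** A reader might infer that the dose figures in general are wrong. They are not: the counts per 2 mL and their SDs reproduce, the table labels them per 2 mL, and the arms are produced by preparation method rather than by a fold rule. Only the fold column and the text's per-patient definition are at fault.

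**The position against the 3–5-fold window hardly changes.** It is tempting to say that Group 1 really lies inside the window rather than across its lower edge. The recomputed range starts at 2.90, so it still crosses 3, and Group 2 crosses 5 on either set of figures. What changes is the share of each range inside the window: more for Group 1, less for Group 2.

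**Doubling a constant leaves a correlation unchanged.** This is correct. The single-session rule matters only for patients who receive one session, or where the two preparations differ in count. The article gives no figure for either.

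**Pooling is not stated.** A reader might infer that composition will be correlated with outcome across both arms. Section 2.3.1 does not say so, and section 2.8.4 specifies only cytokine–outcome correlations. Leaving this detail to an analysis plan is no fault, so step 4 of the working is conditional.

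**The stated aim is already a composite comparison, and mechanism is deferred to in vitro work.** This is true of the Abstract, the Introduction and the close of the Discussion. The two component-level sentences in the Discussion remain and conflict with that aim, although they enter no planned test.

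**Conclusion.** The concern holds in three limited parts.

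1. The stated fold ranges are inconsistent with Table 1's means and its 200–300 ×10^9/L reference. They are low by about 0.4 at the lower limits and by 0.8 and 0.6 at the upper limits, and the Discussion repeats them as what the groups are set at. This assumes that the range means group mean over reference, which is the plain reading of the footnote. The number of samples behind Table 1 is not given.
2. The count defined as given to each patient reflects one of two scheduled sessions and ignores the number received. At the Table 1 means a two-session course is twice the defined figure.
3. The Discussion's claims about the role of each component and about synergy exceed what two arms differing in both components can identify. This holds whether or not any correlation is pooled.

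Nothing here touches the primary ANCOVA in section 2.8.3 or the sample size in section 2.7. These are corrections that should be made, and they do not threaten the main comparison.

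**What to change.** - **Fold ranges.** Reconcile the Table 1 ranges, the footnote reference and the Discussion, stating the rule used. Alternatively, compute fold per patient from the whole-blood and PRP counts that section 2.3.1 already has measured. Which figures describe the intended product is for the sponsor to state, and no dose is proposed here.
- **Platelet count.** Label the Table 1 count as per session. For the correlation analysis, sum the measured counts over the sessions actually given.
- **Composition–outcome correlation, if done.** Run it within arm or adjusted for arm.
- **Discussion wording.** Limit conclusions to the comparison of the two composite formulations and remove the claims about component roles and synergy.

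The cost is corrected figures and wording plus a defined exposure variable, with no new data collection. The downside is that each within-arm correlation rests on fewer patients, and with almost no within-arm WBC spread it can say little about leukocytes.

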#### Standardization of injection timing

2.3.2

The timing of PRP injection, from the diagnosis of RCI to the first injection, will be standardized for all participants. The injury occurrence time is defined as the exact date when shoulder pain and motor dysfunction first appeared. For patients with an insidious onset, the injury occurrence time is defined as the date of MRI confirmation of RCI. The injection date will be recorded on the exact day to calculate the injury-to-injection time interval (days). For patients with subacute RCI (symptom duration 2–6 weeks), those with an injury-to-injection time interval of 0–2 weeks are included in the first subgroup, while those with a 2–4 week interval are included in the second subgroup, ensuring a balanced distribution between the two groups. The mean injury duration and injury-to-injection time interval will be recorded at baseline and compared between the groups. If significant differences are detected, these variables will be included as covariates in statistical analysis.

